**Lifestyle habits**										
Diet quality	C-HEI 2007 score measured with the R24W	•	•		•	•	•	•	•	
Diet quality	Urine dietary exposure biomarker profile	♀	♀					♀		
Physical activity	IPAQ	•		•		•	•	•	•	
Active minutes and step count	7-day Fitbit recording	•		•		•	•	•	•	
Sleep quality	PSQI	•		•		•	•	•	•	
Anxious and depressive symptoms	HADS	•		•		•	•	•	•	
Quality of life	SF-12	•		•		•	•	•	•	
Attitude toward behavior change	Homemade questionnaire	•		•		•	•	•	•	
**Anthropometric measures**										
Height	Stadiometer	•								
Weight	Calibrated scale	•		•		•	•	•	•	
Body fat percentage	Foot to foot bioimpedance	•		•		•				
Waist circumference	Measuring tape	•		•		•				
**Pregnancy outcomes**										
Last weight before delivery	Patient medical record									♀
Gestational diabetes	Patient medical record									♀
Hypertensive disorder of pregnancy	Patient medical record									♀
Gestational age at delivery	Patient medical record									♀
Delivery mode	Patient medical record									♀
**Neonatal outcomes**										
Birthweight	Patient medical record									♀
Neonatal hypoglycemia	Patient medical record									♀
**Fertility outcomes**										
Clinical pregnancy rate	Patient medical record									♀
Spontaneous abortion rate	Patient medical record									♀
Live birth rate	Patient medical record									♀

*•: Evaluated for both partners. ♀ and 

: Evaluated for the woman attempting pregnancy or partners only, respectively*.

#### Lifestyle Habits

##### Diet Quality

Diet quality will be measured using the *Canadian Healthy Eating Index* 2007 (C-HEI 2007) which is a 100-point score adapted from the American HEI-2005 to measure adherence to the 2007 Canadian Food Guide (57, 58). The C-HEI 2007 score will be measured at baseline, 2, 4, and 6 months in preconception and each trimester in pregnancy with the *R24W*, an online 24-h dietary recall tool available in French and English, and validated for both pregnant and non-pregnant individuals of the French-Canadian population (59, 60). Three dietary recalls will be used to compile the C-HEI score at each time point, two recalls of weekdays and one recall of a weekend day. On the day the 24-h recall is to be completed, an e-mail will be sent to the participant. If the participant fails to complete the R24W, subsequent e-mails will be sent, within 3 weeks (or within the trimester), until three R24W are completed. Detailed reports of energy, macro and micronutrient, are automatically derived from the recall and will also be compiled and analyzed. Furthermore, a new diet quality index reflecting the 2019 Canadian Food Guide might become available to assess diet quality and will be reported if applicable.

Women's urinary dietary exposure biomarker profiles will be analyzed as a secondary assessment of diet quality. A crossover randomized controlled trial published in 2017 demonstrated that urinary metabolic profiling is a precise tool to evaluate dietary intake of the preceding 72 h, that it is sensitive to change, and that it correlates well with the DASH dietary index (61). Participants will collect urine samples on three random days over 1 week at the designated time frame. These spot samples will be pooled after normalizing using refractive index measurement to guide dilution. Around 40 metabolites will be targeted for the quantitative measurement of dietary intake biomarker concentrations. The concentration of dietary intake biomarkers will be measured using Multiple Reaction Monitoring (MRM) methods on a Triple Quadruple LC-MS/MS instrument (47). Each metabolite can be associated with the consumption of a specific food. These foods will then be grouped together into Healthy Eating Index categories to compute a relative dietary quality score (48).

##### Physical Activity

Physical activity behavior will be assessed at each research visit using the *International Physical Activity Questionnaires* (IPAQ) (62).

##### Active Minutes and Step Count

The minutes of moderate to intense physical activity and the daily step count will be measured after each research visit using a 7-day Fitbit recording (Flex 2 model). The use of the Fitbit monitor to measure these variables has been validated both in the general (63, 64) and pregnant population (65).

##### Sleep Quality

Sleep quality will be evaluated after each research visit using the *Pittsburgh Sleep Quality Index* (PSQI) (66).

##### Anxious and Depressive Symptoms

The intensity of anxious and depressive symptoms will be evaluated at each research visit with the *Hospital Anxiety and Depression Scale* (HADS). Both the anxiety (HADS-A) and depression (HADS-D) dimensions of this scale have been extensively validated in the general (67) and gynecological population (68). This questionnaire can also be utilized as a screening tool for anxious and depressive disorders with a cut-off value of 8 or greater on the HADS-A or HADS-D subscales (67, 68).

##### Quality of Life

Quality of life will be evaluated at each visit using the SF-12, a shortened version of the SF-36 which evaluates both physical and mental health and has been validated in the gynecological population (69).

##### Attitude Toward Behavior Change

The readiness, conviction, and confidence of study participants to change their diet and physical activity will be measured using a 22-item questionnaire. This questionnaire was designed for previous studies (70, 71) at our center and is based on Prochaska and DiClemente's transtheoretical model of change (72).

##### Anthropometric Measures

All anthropometric measures will be performed by a research assistant who has been trained in these measures based on WHO standards (73).

#### Pregnancy Outcomes

##### Total Weight Gain in Pregnancy

Total weight gain in pregnancy will be calculated by subtracting the woman's weight at the last attended preconception visit from the last weight recorded before delivery. The last weight recorded before delivery will be obtained from the patient medical record. Trimester specific weight gain velocity will also be calculated based on the weight measured at the research visits. Trimester-specific gestational weight gain will also be computed using previously described methodology (74). Both total and trimester specific weight gain will be compared to the NAM recommendations (46).

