### Hypothesis

*Healthy for my Baby* is a novel behavioral intervention developed by our research team to support the adoption of healthy lifestyle habits for women with overweight or obesity, and their partners, in preconception and throughout pregnancy. Our hypothesis is that, compared with standard preconception and obstetrical care, this intervention will lead to:

An improvement in the lifestyle habits of women and their partners in the preconception period and during pregnancy.A reduction in women's weight in the interval from enrolment to either (a) occurrence of a pregnancy or (b) in the absence of pregnancy, 6 months of follow-up.

Among women who achieve pregnancy, we also aim to generate preliminary data on the effect of the intervention on the proportion of women who adhere to gestational weight gain guidelines as well as on rates of complications in pregnancy and the neonatal period.

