## Methods and Analysis

### Objectives

In accordance with the Obesity Related Behavioral Intervention Trials Consortium model for the development and evaluation of interventions, the primary aim of this study is to determine the impact of the intervention on disease risk factors (40). This trial will be conducted in two phases. The preconception phase will evaluate the impact of the intervention on preconception risk factors for pregnancy, neonatal, and metabolic complications, which include lifestyle habits and anthropometric measures. These outcomes will provide an insight on the mechanisms through which the intervention might improve clinical outcomes. The pregnancy phase will evaluate whether the intervention has a sustained impact on lifestyle habits, and will allow us to obtain preliminary estimates of potential impacts on clinical maternal and neonatal outcomes.

The primary outcome of the trial is the diet quality of women, assessed with the Canadian Healthy Eating Index (C-HEI) during the preconception period, as it is sensitive to change and has been identified as an independent predictor of gestational diabetes, hypertensive disorders of pregnancy, birthweight, and neonatal fat mass (41–44). This outcome is also associated with parallel changes in other behaviors, such as physical activity, sleep, well-being and environment, which are however less sensitive to change over a relatively short period. Since this trial is the initial evaluation step in the evaluation of a novel intervention, we have chosen to base the power of the trial on this disease risk factor, with all other outcomes being secondary at this point.

We set the maximum duration of preconception follow-up at 6 months as fertility rates tend to plateau or decline after 6 months of attempting to achieve pregnancy (45).

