**For the Preconception Period:**

The primary objective of this trial is to evaluate the impact of the intervention on the diet quality of women measured with the Canadian Healthy Eating Index at 2, 4, and 6 months of follow-up.The secondary objectives of the preconception period are to evaluate the impact of the intervention on:- Urinary metabolomic indicators of women's dietary exposure at 2 months follow-up,- The diet quality of male partners at 2, 4, and 6 months follow-up,- The other lifestyle habits of women and their partners at 3 and 6 months (physical activity, sleep quality, anxious and depressive symptoms, and quality of life),- The anthropometric measures of women and their partners at 3 and 6 months (weight, waist circumference, and body fat percentage), and- The proportion of women and partners with a weight loss of at least 5% body weight at 3 and 6 months.

After completion of the primary outcome assessment, women and their partners who have achieved a pregnancy within 12 months following enrolment will be followed until the end of the pregnancy. Although, there is a potential for unbalanced study groups if the intervention has an impact on fertility, this exploratory follow-up phase will provide preliminary data on the impact of the intervention on lifestyle and clinical outcomes in pregnancy.

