### Variables and Data Collection

Participants' medical history and socioeconomic status will be evaluated at baseline. Women and their partner's diet quality will be measured with 24-h dietary recalls at baseline, 2, 4, and 6 months in preconception and at 6–8 weeks, 24–26 weeks, and 32–34 weeks in pregnancy. Women will provide urinary samples for the metabolomic analysis at baseline and 2 months in preconception and at 24–26 weeks in pregnancy. Women and their partner's other lifestyle indicators (physical activity, sleep, anxious, and depressive symptoms, quality of life, and attitude toward behavior change), and anthropometric outcomes will be evaluated at baseline, 3 and 6 months in preconception and every trimester in pregnancy. Information on pregnancy and neonatal outcomes will be collected from participants' medical records at the end of the study. The study variables, measuring tools, and the timing of data collection have been summarized in Table 1.

**Table 1 T1:** Summary of study variables.

		**Timing of data collection in preconception (months)**					**Timing of data collection in pregnancy (weeks of amenorrhea)**			
**Variables**	**Measuring Tool**	**0**	**2**	**3**	**4**	**6**	**6-8**	**24-26**	**32-34**	**End of study**
Medical history	Homemade questionnaire	•								
Socioeconomic status	Homemade questionnaire	•								

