#### Secondary Outcome Analysis

For the main secondary outcome for the pregnancy phase of the trial, we will use a Chi-squared test to compare the proportion of women who have an adequate gestational weight gain in each group.

For the targeted analysis of urine biomarkers, the concentration of around 40 metabolites will be compared between baseline, 2 months in preconception and 24–26 weeks of pregnancy using repeated measures ANOVA or Friedman test with a Bonferroni adjustment for multiple comparisons. The correlation between the metabolite derived diet quality score and the C-HEI score will be evaluated using Pearson's correlation.

Although our sample size is fairly small, an exploratory multivariate analysis of non-targeted metabolome profiles will be realized using both unsupervised ‘natural clustering’ analysis and Supervised Random Forest classification.

For the other secondary outcomes, continuous variables will be assessed using Student's *t*-tests or Mann-Whitney tests as appropriate. Dichotomic variables will be analyzed using Chi-squared tests or Fisher's exact test as appropriate.

For participants who achieve a pregnancy prior to the 2-month food recall and/or 3-month preconception visit, lifestyle and anthropometric outcomes at the first pregnancy visit will be used to complete the preconception analysis. Women will be able to signal the occurrence of a pregnancy through the mobile application as soon as a period is missed. The application software will immediately notify the research team which will allow completion of data collection prior to the occurrence of significant pregnancy symptoms such as hyperemesis.

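### Total gestational weight gain starts from the last attended preconception visit, so weight change between that visit and conception is counted as gestational change, and this can differ by arm

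*Protocol article*

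**What the plan says.** All references are to the Protocol article.

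- **Definition (Total Weight Gain in Pregnancy).** Total gain is "calculated by subtracting the woman's weight at the last attended preconception visit from the last weight recorded before delivery". Trimester-specific gain is also computed, and both are compared with the guideline.
- **Weight schedule (Variables and Data Collection; Table 1).** "anthropometric outcomes will be evaluated at baseline, 3 and 6 months in preconception and every trimester in pregnancy". Table 1 lists weight at 0, 3 and 6 months, then at 6–8, 24–26 and 32–34 weeks of pregnancy.
- **Length of follow-up (Objectives).** "We set the maximum duration of preconception follow-up at 6 months".
- **Pregnancies included (For the Preconception Period).** Couples who have "achieved a pregnancy within 12 months following enrolment will be followed until the end of the pregnancy".
- **Expected effect (Hypothesis).** Relative to standard care, the intervention should produce "A reduction in women's weight in the interval from enrolment to either (a) occurrence of a pregnancy", or over 6 months if there is none.
- **Analysis (Secondary Outcome Analysis).** For the main secondary outcome of the pregnancy phase, "we will use a Chi-squared test to compare the proportion of women who have an adequate gestational weight gain in each group". The same section says that, for women who conceive before the 2-month recall or the 3-month visit, measurements from the first pregnancy visit complete the preconception analysis.

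**The concern.** Gestational gain should measure change from conception onwards. Here it is measured from a visit that may lie months earlier. Whatever weight a woman loses or gains between that visit and conception is booked as pregnancy weight change. The trial hypothesises that the intervention lowers weight in the preconception interval, so the error is expected to differ between arms if the intervention works.

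The exposure is plainest for women who conceive before month 3, because their starting weight is the enrolment weight. For these women there is a second difficulty. Their first pregnancy visit completes the preconception analysis, while the gain definition still runs from enrolment. The same kilograms can then appear both as preconception loss and as lower gestational gain.

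At stake is the interpretation of the main secondary outcome of the pregnancy phase. That phase is meant to supply preliminary data for a larger trial, and part of a preconception effect could be read as an effect on gestational gain.

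**Working it through.** The article states no figure for gestational gain, so there is none to reproduce. The gaps follow from its schedule. The kilogram figures need assumptions, which are marked.

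**1. Gap between starting weight and conception, if all visits are attended**

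| Conception (months) | Starting weight taken at | Largest gap (months) |
|---|---|---|
| 0–3 | enrolment | 3 |
| 3–6 | month 3 | 3 |
| 6–12 | month 6 | 6 |

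The rule takes the last *attended* visit. A woman who misses both the 3- and 6-month visits could have a gap of up to 12 months.

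**2. What enters recorded gain**

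Recorded gain = true gain + (weight at conception − weight at last attended visit).

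Only change after that visit enters. Loss already present at month 3 or 6 lowers the starting weight and does no harm.

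**3. Average gap (assumed constant monthly conception probability, truncated at month 12)**

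| Monthly conception | 5% | 10% | 15% |
|---|---|---|---|
| Share conceiving before month 3 | 31% | 38% | 45% |
| Share conceiving after month 6 | 42% | 35% | 27% |
| Mean gap, conceptions before month 6 (months) | 1.46 | 1.42 | 1.38 |
| Mean gap, conceptions after month 6 (months) | 2.85 | 2.69 | 2.52 |
| Mean gap overall (months) | 2.05 | 1.86 | 1.69 |

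**4. Average error in recorded gain**

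Assumed arm difference: 5% of an assumed 85 kg over 6 months, i.e. 0.05 × 85 / 6 = 0.71 kg per month. The 5% is borrowed from the article's individual weight-loss threshold. It is not a stated expected mean.

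- Conceptions before month 6: 0.71 × 1.38 to 1.46 = about 1.0 kg too low.
- All conceptions, loss stops at month 6: 0.71 × (share before month 6) × (their mean gap). At 5% this is 0.71 × 0.576 × 1.46 = 0.60 kg; at 10%, 0.66 kg; at 15%, 0.71 kg.
- All conceptions, loss continues to month 12: 0.71 × overall mean gap = 1.45, 1.32 and 1.20 kg. The individual maximum is 6 × 0.71 = about 4.3 kg.
- Half of the loss regained by month 12: about 0.17, 0.33 and 0.46 kg. Among conceptions after month 6 the error reverses sign.
- A smaller effect, 2 kg lost over 6 months and then a plateau: about 0.3 kg.

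**5. Effect on the tested proportion**

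Illustration with assumed true gain (mean 8–12 kg, SD 5–6 kg), assumed target bands of 5–9 or 7–11.5 kg, conception spread evenly over 12 months, and 2–4 kg lost by month 6 followed by a plateau:

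- Share above the band: falls by about 1.4–4.0 points on average, and by 5–16 points for a woman at the full 3-month gap.
- Share inside the band: moves by −1 to +2 points on average, and by −5 to +7 points at the full 3-month gap.

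A lower recorded gain moves some women from excessive to adequate and others from adequate to inadequate, so the net shift has no fixed direction.

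**6. The two rules side by side, for a conception at month 2.5**

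At 0.71 kg per month the woman has lost 2.5 × 0.71 = about 1.8 kg by conception. Total Weight Gain in Pregnancy starts from enrolment, so recorded gain is 1.8 kg too low. Secondary Outcome Analysis takes her first pregnancy visit as the preconception outcome, so the same loss also counts there.

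**The case against.** The case on the other side is substantial, and much of it stands.

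- **Not all preconception loss is affected.** A reader might infer that any weight the intervention removes before pregnancy is counted as low gestational gain. The definition does not do that. Loss recorded at the last attended visit is already in the starting weight. Nor is the error confined to one arm: control women's weight can also change in the gap, and only the difference matters.
- **The larger figures are one-sided.** The 1.2–1.5 kg mean and the maximum above 4 kg need undiminished loss to month 12. Nothing in the article supports that. Preconception follow-up is capped at 6 months, and the scheduled contacts are two interviews plus at most two further monthly sessions.
- **No direction is shown for the endpoint.** Adequate gain is a range, so the tested proportion can shift either way, and on average by little.
- **Related complaints do not hold.** The article does not say which weight sets the BMI class for the guideline, so an error there is inference. Preconception weight change is already an objective of its own. The article itself warns that groups may be unbalanced among women who conceive and calls this phase exploratory. Replacing the chi-squared test with an adjusted comparison is a preference and would not remove selection on conceiving.
- **Trimester-specific gain is less exposed** in later trimesters, because it uses research-visit weights. The analysis section does not say whether the test uses total or trimester-specific gain.

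None of this removes the carry-over in total gain or the conflict between the two rules for early conceptions.

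**Conclusion.** The point holds in a limited form. Weight change between the last attended preconception visit and conception is counted as gestational change, over up to 3 months for conceptions before month 6 and up to 6 months afterwards (longer with missed visits). It differs by arm if the hypothesised preconception weight loss occurs. For conceptions before the 3-month visit, the same loss can be counted in two outcomes.

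On an assumed 0.7 kg per month and 5–15% monthly conception, the mean error in recorded gain is about 0.6–0.7 kg if loss stops at month 6, 1.2–1.5 kg if it continues to month 12, and less with regain. These are illustrations, because the article gives no expected weight loss, gain distribution or target range. A reader might conclude that the main pregnancy endpoint is biased in favour of the intervention. The material does not support that, because the sign for the proportion with adequate gain is open. What is affected is how the result can be interpreted.

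The primary outcome, its sample size and its analysis are unaffected. This is a lower-priority, inexpensive improvement rather than a condition for going ahead.

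**What to change.** 1. In Total Weight Gain in Pregnancy, define the starting weight as weight at conception, interpolated between the last attended preconception visit and the 6–8 week research weight already in Table 1.
2. As sensitivity analyses, report total gain from the 6–8 week weight itself and from the current definition.
3. Reconcile that section with Secondary Outcome Analysis for women who conceive before the 3-month visit, so that the same kilograms are not counted both as preconception loss and as lower gestational gain.

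**Cost.** A wording change and a little analysis work, with no new weight measurement. Each woman needs an estimated conception date.

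**Downsides.** Interpolation assumes linear change. If weight stops falling at conception, part of the error remains. In the month-2.5 example, with the pregnancy weight taken an assumed 1.15 months after conception and weight flat in between, interpolation recovers 2.5 / 3.65 = 68% of the 1.8 kg and leaves about 0.6 kg. Starting at 6–8 weeks removes the preconception carry-over but omits early-pregnancy change. That change may differ by arm, because the intervention is intensified with interviews at 6–8 and 10–12 weeks. This is why the 6–8 week weight is better as a sensitivity analysis than as the sole definition.

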##### Pregnancy Complications

The diagnoses of gestational diabetes or hypertensive disorders of pregnancy, gestational age at delivery, and delivery mode will be compiled from women's medical records based on *International Classification of Diseases-Tenth Revision* codes.

